### **7.3.3 Further details for statistical analyses**

Baseline characteristics that are quantitative measurements will be checked across the range of measures as part of data cleaning prior to statistical analysis. This will ensure that perceived outliers are not data entry errors. A genuine outlier will be defined as a measurement that is

greater than three standard deviations from the mean; on a log-transformed scale if measurements are approximately log-normally distributed on their original scale. Regression diagnostics will be used to assess the influence of genuine outliers on treatment comparisons in analyses that include a quantitative baseline characteristic. Where outliers are found to exert such an influence, a secondary analysis will be performed with the outliers removed and the results of the two analyses will be reported.

#### **7.3.4 Pre-specified sub-group analyses**

Pre-specified analyses will be undertaken within sub-groups where there may be a difference in the net benefit of aspirin from the remainder of the population. These sub-group analyses will utilize appropriate interaction terms in Cox proportional hazards regression models. The p-values for these interaction terms will be used to test for heterogeneity of treatment effect of aspirin between sub-groups. These sub-groups include:

- a) **Males versus females:** Recent data from the Women's Health Study (WHS) showed a significant reduction in vascular events in females aged 65 years and over. A meta-analysis suggested that amongst younger females the principal effect of low-dose aspirin is to reduce the risk of stroke with little effect on MI except in those aged 65 years and above, whereas in males the effect is a reduction of MI with minimal effect on stroke.
- b) **Age below and above study median** (expected to be approximately 75 years): The balance of risks and benefits due to aspirin may differ between age groups as a result of different rates of mortality, cardiovascular risk, cognitive decline, other disability and risk of adverse effects (as defined for our secondary objectives).
- c) **Country:** U.S. versus Australia.
- d) **Ethnicity:** Whites versus African Americans versus Hispanics versus other (where 'other' will include Native Americans, Asians and Aboriginal Australians).
- e) **Diabetes:** The presence or absence of a diagnosis of diabetes at baseline.
- f) **Hypertension:** Hypertensives versus non-hypertensives. Hypertension is defined as those who are on treatment for high blood pressure or those with blood pressure recorded above 140/90 mmHg at study entry.
- g) **Smoking:** Current versus Never or Former smokers.

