## 10 SAMPLE SIZE AND POWER CALCULATIONS

Participants will be approximately two-thirds from Australia and one-third from the U.S and will include 4,500 minority participants. There will be an equal allocation of participants to aspirin and placebo groups. A detailed description of sample size and power calculations for the primary and secondary endpoints is provided in Appendix 2.

In brief, 19,000 participants having 3787 events will be required to have 90% power (two-sided alpha error rate of 0.05) to detect a 10% reduction (risk ratio of 0.90) in the primary endpoint with aspirin. The rationale for this effect size is described in Appendix 2. This sample size was calculated for a univariate Cox proportional hazards regression analysis using Stata (Stata Statistical Software, Release 10, StataCorp, College Station, TX, 2007) and based on the following assumptions:

- a. The effect of aspirin is described by a hazard ratio of 0.90 in an intention-to-treat analysis. This assumes a slightly stronger underlying effect that will be weakened by cross-over of participants for reasons which include the development of a non-fatal, non-disabling cardiovascular or cerebrovascular events necessitating aspirin therapy or cessation (non-compliance) with aspirin therapy. We expect 5% per annum of placebo-group participants to initiate aspirin use (or *vice versa*).
- b. Annual dementia incidence rates of 6 per 1000 for 70-74y age group, 11/1000 (75-79y), 20/1000 (80-84y), 37/1000 (85y+)  for Australian, U.S. Hispanic and U.S. White (non-Hispanic) participants. For U.S. African Americans the rates are doubled .
- c. Incident disability for one or more Katz ADL's; annual incidence rate for males= 19.6/1000, females = 26.5/1000 (these incidence rates are from the rates observed in the subset of

- ASPREE-like participants in the CHS ([name], personal communication, August, 2008) which showed similar rates in U.S. Whites and U.S. minorities).
- d. Age-specific mortality rates in Australian and U.S. White (non-Hispanic) participants are based on the 2004 Australian population census (<http://www.aihw.gov.au/mortality/data>). Age-specific mortality rates in U.S. African American and Hispanic participants are based on 2005 rates specific to each minority (U.S. CDC statistics, 2005; <http://www.cdc.gov/nchs>).

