- e. To allow for the analysis to be time-to-first event, individual rates for death, ADL loss and dementia can be summed and the sum reduced by 10% to allow for the potential for different events to occur in the same individual .
- f. Participants will be 45% male and 55% female.
- g. The cohort will consist of 50%, 30%, 15%, 5% in age groups 70-74 years, 75-79 years, 80-84 years, 85 years and over, respectively.
- h. The average at risk time will be 4.25 years per participant which allows for censoring due to the primary endpoint or non-completion of dementia screen or diagnosis, and non-completion of ADLs.

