## **8. Major hemorrhagic events**

We anticipate rates of major bleeds of 11 events per 1000 person-years in the placebo group based on:

- Hemorrhagic stroke rate of 1.2 per 1000 person years .
- Serious upper GI complications: between 2 and 14 events per 1000 person-years for those over 70 years, increasing sharply with age .

**Given a total sample size of 19,000, we have 90% power to detect a hazard ratio of 1.23 comparing the aspirin group with placebo in an intention-to-treat analysis where compliance with medication and drop-out are assumed as for the primary endpoint.**

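### Section 7.3.4(b) names only a median split to test whether the treatment effect varies with age; a continuous-age interaction specified alongside it would usually be more powerful, at almost no cost

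*Protocol*

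**What the plan says.** Protocol section 7.3.4 lists seven pre-specified sub-group factors, to be analysed with interaction terms in Cox models. Item (b) sets two age groups, cut at the study median: "expected to be approximately 75 years): The balance of risks and benefits due to aspirin may differ between age groups". On testing, the section says "The p-values for these interaction terms will be used to test for heterogeneity of treatment effect of aspirin between sub-groups". The list opens with "These sub-groups include", so it is not formally closed, but the protocol names no continuous or multi-band age-by-treatment analysis anywhere.

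The reason given in item (b) is that the balance of risk and benefit may differ because several event rates differ with age. Appendix 2, on major hemorrhagic events, describes serious upper gastrointestinal complications as "increasing sharply with age". Neither place says why any change should fall at the median. The randomization strata in sections 2 and 7.1.4 cut age at 80, not at 75.

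The protocol gives no interaction effect size, no interaction power and no assumed shape for the effect of age on the hazard ratio.

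**The concern.** Splitting a continuous effect modifier at its median treats everyone on one side of the cut as alike. If the treatment effect drifts with age, the split ignores the drift within each half. Under the section 10 age mix, 30 of every 50 participants in the upper half are aged 75-79. A change confined to those over 80 is therefore diluted by the majority of the group it is tested in.

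What is at stake is power for one sub-group question. A gradient in the treatment effect across the over-70s could go undetected by the named test when the same data, with age kept on its scale, would show it. Adding a continuous-age test after unblinding would be open to the charge that the age scale was chosen to suit the result.

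**Working it through.** **Reproducing the plan's own figures.** Section 10 states "19,000 participants having 3787 events will be required to have 90% power (two-sided alpha error rate of 0.05) to detect a 10% reduction". With the Schoenfeld formula, events = 4(1.96 + 1.2816)² / (ln 0.90)² ≈ 3,787, which matches. Appendix 2 later gives 3,374 + 311 = 3,685 events for 89% power. The same formula gives Φ(½√3685 × |ln 0.90| − 1.96) = 89.2%.

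**Inputs for the age calculation.**
- Age mix, section 10: "The cohort will consist of 50%, 30%, 15%, 5% in age groups 70-74 years, 75-79 years, 80-84 years, 85 years and over, respectively".
- Appendix 2 rates: dementia 6, 11, 20, 37 per 1000. Mortality by sex and age, halved and weighted 45% male, 55% female: 10.0, 17.6, 31.2, 70.6 per 1000. ADL loss 0.45 × 19.6 + 0.55 × 26.5 = 23.4 per 1000.
- Sum reduced by 10%, as Appendix 2 specifies.

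**Rates and event shares.** Band rates = 0.9 × (mortality + dementia + ADL loss) = 35.5, 46.8, 67.2, 117.9 per 1000, or 47.7 overall. Multiplying by 0.95 (the average of two arms at hazard ratio 0.90) gives 45.4, the figure in Appendix 2. The shares of events are 37%, 29%, 21%, 12%.

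**Efficiency of the split.** If the log hazard ratio is linear in age, the relative efficiency of the split is the squared correlation between the over-75 indicator and age, weighted by events.
- Band midpoints 72, 77, 82, 87: efficiency 0.653, event-weighted age SD 5.17 years, loss about 35%.
- Ages spread within bands with a short tail above 85: efficiency 0.604, loss about 40%.
- Spread ages weighted by participants instead of events: efficiency 0.646.
- Other assumptions about ages within bands: losses from 29% to 46%.

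**Power with 3,685 events.** With slope b in log hazard ratio per year, z = b × 5.17 × ½√3685 for the continuous term. Multiply by √0.653 for the split. Power = Φ(z − 1.96).

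| Slope per 10 years | Continuous | Median split | Loss (points) |
|---|---|---|---|
| 0.05 | 12% | 9% | 3 |
| 0.10 | 35% | 24% | 10 |
| 0.15 | 65% | 48% | 18 |
| 0.20 | 88% | 72% | 16 |
| 0.25 | 98% | 89% | 9 |

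With efficiency 0.604 the losses are somewhat larger. A Poisson-regression simulation (400 replicates, about 3,650 events) at a hazard-ratio ratio of 1.22 per 10 years, a slope of about 0.20, gave 91% vs 70%.

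**If the change is a step instead.** The share of the available information that each test keeps, using the same event weights and band midpoints, is:

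| Step at | Median split | Linear term |
|---|---|---|
| 75 | 100% | 65% |
| 80 | 30% | 77% |
| 85 | 8% | 48% |

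With ages spread within bands, the linear term keeps 60% for a step at 75 and 71% for a step at 80. For a step at 75, a split with 80% power then corresponds to 59% for the linear term, and 90% corresponds to 71%.

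**A mismatch in the inputs.** The 3,685 events are the figure after the 2011 recruitment change, while the age mix is the original one. Appendix 2 revises the age mix for U.S. participants only. That moves the median to just under 75 and has little effect here.

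**The case against.** The strongest case against is that this is ordinary practice at protocol level. A median split gives two balanced, readable groups with a proper interaction test, the list is open, and the functional form can be settled in a statistical analysis plan that is not shown. Nothing in section 7.3.4 is wrong or contradictory. This stands: the point concerns what the protocol names, and the trial may yet include a continuous analysis.

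Second, the loss is conditional. It needs a roughly linear log hazard ratio and a slope large enough to detect, and the protocol states neither. The larger slopes are demanding. At 0.20 per 10 years, centred on 0.90 at age 77, the hazard ratio would run from about 0.81 at 72 to about 1.10 at 87, in a trial designed around a 10% reduction overall. With a step near 75 the ordering of the two tests reverses. This also stands, and is why the figures are given as a range with their assumption.

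Three stronger readings are tempting, and the documents do not support them.
- A reader might infer that age is the trial's most important effect modifier. Section 1.2.2 contrasts people over 70 with the middle-aged. It does not single out a gradient within the over-70s, and section 7.3.4 does not rank its seven factors.
- A reader might take the 2.5-fold rise in expected rates between the 75-79 and 85+ bands (46.8 to 117.9 per 1000), or the rise in bleeding with age, as evidence that the hazard ratio changes with age. These are anticipated event rates without aspirin. They say nothing about the ratio.
- A reader might conclude that the median split should be dropped. That would exchange one assumed shape for another. The case is for adding the continuous term.

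**Conclusion.** The point holds as a low-cost improvement. The median split is the only age heterogeneity test the protocol names, and the protocol gives no reason to expect a change there. Under a linear gradient the split loses about 35-40% of the interaction information. The power cost peaks at about 16-18 points for slopes of 0.15-0.20 per 10 years and is small for weak gradients. For a step change at 80 or 85 the linear term is also clearly better. The split is better for a step at or near 75.

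These results rest on the Appendix 2 rates, the section 10 age mix, 3,685 primary events and assumed slopes. They apply to the primary endpoint. No corresponding calculation was made for major hemorrhage. The main treatment comparison is unaffected.

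**What to change.** In section 7.3.4(b), add a Cox model for the primary endpoint with age as a continuous main effect and a treatment-by-continuous-age term. State in advance that the p-value of this term is the age heterogeneity test. Keep the hazard ratios below and above the median, with their interaction, as the display.

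The cost is one or two sentences and one extra model, with no new data. The downside is the assumption of an approximately linear gradient: power is lost if the true change is a step near the median. Keeping the split in the report lets readers see such a pattern.

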## **7.4 Dissemination and implementation of results**

### **7.4.1 Objectives**

Implementation of a theoretically based dissemination intervention, similar to that of the Antihypertensive and Lipid-Lowering Heart Attack Trial (ALLHAT).

- a) To increase awareness of the ASPREE trial by disseminating results via repetitive messages through scientific and professional channels.
- b) To provide physicians, physician's assistants, practice nurses and nurse practitioners with cues to action via distribution of office posters, prescription cards, and other educational materials.

### **7.4.2 Approach and methods**

The following represents various strategies to disseminate study findings and recommendations.

- *Web site.* The ASPREE web site will provide information to the professional and scientific community as well as to the public regarding study results and recommendations (in addition to providing a means by which authorized ASPREE personnel can send data, using electronic CRFs). The web site will consist of published journal articles, newsletters, presentations, a frequently asked questions (FAQs) section, links to other appropriate web sites, and downloadable information for PDAs, iPhones and other devices.
- *Publication.* Study findings and recommendations will be published in appropriate scientific journals to be made available to the scientific community.
- *Slide presentations.* PowerPoint presentations will be constructed to provide study rationale design, results, and implications. These will be available for formal presentations, office or departmental seminars, grand rounds, or local medical society meetings. Select PowerPoint files, i.e. major outcomes, will be available in other languages, including Spanish. Files will be accessible via the ASPREE web site. A set of PowerPoint presentations will also be developed for consumers.
- *Formulary systems approach.* Similar to the ALLHAT dissemination, pre-identified formulary systems will receive a summary of study findings, recommendations, relevant articles, cost-effectiveness information, and strategies for implementation to improve care.
- *Clinical guidelines.* Recommendations in guidelines will assist the facilitation of the dissemination intervention. For example, the ASPREE study results may be reinforced by

the existing US Preventive Task Force and American Heart Association guidelines for the evaluation, prevention and management of cardiovascular disease in adults.

- *Education Materials.* Development of posters, reference cards, and consumer brochures will be effective tools for disseminating study findings and recommendations. Office posters and reference cards will assist sites in management. Consumer brochures will educate the public and provide the necessary information to encourage consumers to speak to their usual health care providers regarding their management.

## **8 STUDY MEDICATION AND SUPPLIES**

### **8.1 Study treatments**

Participants in the study will be allocated to one of two treatments: a) Acetylsalicylic acid (ASA) 100 mg: enteric-coated un-scored white tablet or b) placebo: enteric-coated un-scored white tablet with identical appearance. Study medications are provided by Bayer Pharma AG. A 100mg dosage was selected as this is the common international dose. The enteric coating will ensure that both active and placebo medication have an identical taste.

*Run-in placebo* – A box of placebo medication for 4 weeks will be given to participants at the Lifestyle Profile and Screening visit (Visit 1). If for whatever reason a participant cannot attend their Assessments and Eligibility visit (Visit 2) at 4 weeks, he/she will receive another supply of placebo if it is required for compliance assessment.

*Assessment and Eligibility visit (Visit 2)* – Subsequent to this visit, each participant will be provided with a 12 month's supply of study medication: either aspirin or placebo.

*Annual Visits* – At each Annual Visit each participant will be provided with the next 12 month supply of their allocated study medication. If a participant is unable to attend an annual visit within a month of the scheduled date, and will run out of study medication, the research staff can mail out the medication to the participant provided a new appointment has been scheduled.

### **8.2 Drug packaging**

A bulk supply of enteric-coated active and placebo tablets has been provided free of charge by Bayer Pharma AG. The medication will be packaged and labeled according to the randomization code. Participants will be provided with a 12 month supply on each occasion. Packaging will feature the name of the study (ASPREE clinical trial), sponsor, supplier, batch number, expiry date, contents, the fact that the content is pharmacy medicine for use in clinical trials only, instructions for use, and a warning to keep out of reach of children. Each medication

1100 container will be labeled with a pre-printed, unique medication Identification (ID) Number. Once  
1101 dispensed, this number will also be recorded in the participant's file in the *Study Drug*  
1102 *Accountability Log*.

### 1103 **8.3 Administration of study medication**

1104 One tablet is to be taken daily with advice to take at the same time each day, allowing 24 hr  
1105 between administration.

### 1106 **8.4 Dispensing and randomization**

1107 Medication for the run-in phase will be dispensed to the participant by the study staff at Visit 1.  
1108 Each participant enrolled in the study will be dispensed a box or bottle containing 40 placebo  
1109 tablets. The Practice ID number, Subject ID number and participant's acrostic will be written on  
1110 the container of run-in medication. When the participant returns for the Assessments and  
1111 Eligibility visit (Visit 2), medication compliance will be checked prior to randomization.

1112 Following the completion of the randomization process (Section 7.1.4), in the U.S. a 12 month  
1113 supply of study medication will be provided in person to the participant at the conclusion of the  
1114 visit. In Australia, study medication will be posted to the participant. The participant will be  
1115 asked to confirm receipt of the drug by calling the IVRS automated telephone system. Where  
1116 confirmation of receipt has not been made within 10 days of dispatch of the drug, research staff  
1117 will contact the participant to ensure receipt. Attempts to contact the participant will continue  
1118 until receipt has been confirmed. In the rare instance of missing or undelivered drug, the  
1119 pharmacy will re-issue medication which will be sent for home delivery to the participant.

1120 Subsequent allocation of study medication will be provided in person by research staff at each  
1121 Annual Visit, in both the U.S. and Australia. The Medication ID number assigned to the  
1122 participant will remain the same for the duration of the study. The participant will therefore  
1123 receive study medication with the same Medication ID number at each visit.

1124 One *Study Drug Accountability Log* will be provided for each study participant. These Drug  
1125 Accountability Logs record the drug dispensed to the participant and drug returned from the  
1126 participant.

1127 The *Study Drug Accountability log* will record, at minimum, the following information:

- 1128 • Practice ID number and name
- 1129 • Subject ID Number and participant acrostic
- 1130 • Visit Number

- 1131 • Medication ID number
- 1132 • Date dispensed (initials of dispenser)
- 1133 • Date of medication return (initialed by research staff)
- 1134 • Number of tablets returned
- 1135 • Date of medication destruction
- 1136 • Comments section to allow for explanation of discrepancy, if applicable

## 1137 **8.5 Drug storage**

1138 Upon receipt of the study medication from Bayer Pharma AG, it will be stored at room  
1139 temperature (15-30°C).

1140 All placebo medication for the run-in phase, as well as subsequent years' study medication  
1141 supply, will be distributed to ASPREE sites and stored in a secured area with restricted access,  
1142 at room temperature under the supervision of the site Principal Investigator.

1143 The receipt, storage, dispensing, accountability and study medication collection, for both the run-  
1144 in and randomization phases, are the responsibility of each site's Principal Investigator.

## 1145 **8.6 Drug accountability and dispensing logs**

1146 All medication containers, whether empty or containing unused tablets, must be collected to  
1147 allow medication compliance to be determined (via a pill count) and to allow for proper  
1148 destruction of the medication. Unused tablets are to be returned at the Annual Visit for  
1149 compliance checking and a new supply of study medication will be issued. Lost medication  
1150 packs will be replaced and sent to the participant by mail, with all details recorded to allow an  
1151 audit trail. Tablet counts will be made of all returned medication packs.

1152 Records will be maintained of the product's delivery to each ASPREE site, the use by each  
1153 participant, and the disposition of unused study medication. These records will include dates,  
1154 quantities, batch numbers, expiry dates and the unique Medication ID numbers assigned to the  
1155 investigational product(s) and study participants.

1156 Investigators will maintain records that document adequately that study participants were  
1157 provided the doses specified by the protocol and reconcile all study medication received from  
1158 the drug distribution center. The investigator must verify that all unused or partially used drug  
1159 supplies have been returned by the study participant and that no remaining supplies are in the  
1160 participant's possession. Accurate drug records will be achieved through the use of Dispensing  
1161 Logs.

